### Recruitment & eligibility

#### Setting

This study took place within Galway city and county, in the Republic of Ireland. Recruitment, data collection, intervention and trial management all took place within this region and were coordinated by the primary researcher under the joint supervision of the School of Arts and Social Sciences at City University London and the School of Psychology at the National University of Ireland, Galway (NUIG).

#### Participants

Participants were females with a diagnosis of a mild or moderate intellectual disability who receive support services from the Brothers of Charity Services, Galway. This organisation provides day programmes, residential and respite services, family and multi-disciplinary supports to individuals with intellectual disabilities and to their families. The Diagnostic and Statistical Manual (DSM) framework was used for the diagnoses of intellectual disability and participants IQ scores were in the range 35 – 70.

#### Recruitment strategy

Potential participants who met the inclusion criteria for the study were identified by the Team Leaders for school age and adult services, who have access to such information.

#### Inclusion criteria

Research study participants were females aged between 12 and 30 years of age who have been formally diagnosed using standardized measures of cognitive ability and found to be functioning in the mild or moderate range of intellectual disability. The upper age limit of 30 years was selected to avoid overlap with early menopausal symptoms, as per Kyrkou [7]. Speech was the primary means of communication of research participants. The level of speech of all participants was consistent with their level of intellectual ability, or greater.

Participants were in education or training, attending either a secondary school or an adult training programme. They had commenced menstruation and experienced recurrent pain symptoms with menstruation which impacted on daily functioning.

#### Exclusion criteria

Females were not eligible to participate in the study if they did not have an intellectual disability. Research indicates that cognitive-behavioural strategies may be suitable for individuals with mild and moderate intellectual disabilities and for this reason, individuals with more significant degrees of cognitive impairment were excluded from the study as they would not be able, cognitively, to participate.

In addition, females were not eligible to participate in the study if they were younger than 12 years of age or over 30 years of age, if they had not commenced menstruation, did not experience menstrual pain or if their primary method of communication was via non-verbal strategies.

Participants were not excluded from participating in this research on the basis of ethnicity, race, sexuality, religion or any other socio-cultural factors.

#### Consent

The parents/guardians of potential participants were approached via a participant information letter and asked if they wished to take part in the study and if they consented to their daughter participating in the research. A consent form was provided for this purpose. Once consent was obtained from parents/guardians, assent to participate in the research study was also sought from the young women in question, via a visual participant information sheet and consent form. A copy of these forms was provided to each potential participant and read out to them by the Researcher, at the same time.

### Treatment allocation and matching process

#### Intervention condition

Due to the logistics and practicalities of delivering an intervention group to individuals within a wide geographical sampling area, a non-randomised process was used to assign participants to the intervention group.

A list was compiled of all females attending a special class for students with a mild or moderate intellectual disability or a school for students with mild or moderate intellectual disabilities, who receive support services from the Brothers of Charity Services within County Galway. The Principals of five schools were contacted, informed of the research study and invited to participate in the study. Two schools agreed to participate and were assigned to the intervention group. Parents/Guardians of the relevant students were then contacted and asked for their consent for their daughters to participate. Once consent was granted, assent was obtained directly from the young women.

This treatment allocation methodology allowed for the delivery of the intervention during the school day, at the location where the young women received their day service. This minimised inconvenience and school absence for research participants. This approach also enabled the intervention to be delivered to participants at an appropriate space within the school timetable e.g. during Social, Personal and Health Education (SPHE) class and so ensured consistent attendance.

The same approach was used to recruit participants attending Adult Day Centres providing educational and training opportunities to young women with mild and moderate intellectual disabilities, who receive support services from the Brothers of Charity Services within County Galway.

#### Control condition

Individuals in the control condition were an equivalent comparison group matched by gender, age range and level of intellectual disability. These individuals were invited to participate in the study and were informed that they were allocated to the control condition and what that meant. They were informed that they would be offered the intervention condition, once the study was completed.

### The intervention

#### Programme development

Prior to the main intervention, qualitative preparatory work was completed. Parents/Guardians were invited to take part in a focus group to inform the development of the intervention to best meet the needs of this group of participants. The Participative Research Process (PRP) methodology was chosen for this aspect of the study so that the parents could present their ideas in a “more reflexive, interactive and flexible framework” [26]. The PRP methodology facilitates participants to present their perspectives without filtering or censure by researchers. The PRP allows varying and sometimes unexpected perspectives to emerge as participants create, collate and present their own data. Participants were provided with session outlines of the “*Feeling Better*” programme and asked to consider what should and should not be included in a menstrual pain management programme suitable for their daughters and how this could be done. Parents were asked to respond to a single question: “If your daughter takes part in this group, what would it need to have to help her to cope with menstrual pain?” They then created a ‘web of ideas’ of what they felt was suitable content and delivery methods.

#### Intervention programme

The menstrual pain management intervention programme consisted of twelve sessions:

• Session 1: Psycho-education

• Session 2 – 4: Deep breathing, progressive muscular relaxation and guided visualisation

• Session 5: Taking exercise

• Session 6: Distraction techniques

• Session 7 – 9: How your thoughts make you feel, challenging negative thoughts and using positive coping strategies

• Session 10: Problem solving

• Session 11: Medication

• Session 12: Planning for the future

Each weekly session was conducted with a group of 5–7 young women and lasted approximately 45 minutes. The session structure consisted of a recap of the previous session and feedback on how participants used the new technique, general information, topic related examples, group exercises and discussion, homework exercises and a session summary sheet. At the end of each session, participants interacted during a snack break which fostered a sense of group cohesion.

#### Internal pilot

The intervention was delivered to five participants and assessment measures completed at key time points. The observations and experiences of the researchers during administration of the assessment measures underpinned modifications to some of the wording on some questionnaires to ensure that participants would understand what was being asked of them. Response options and scoring categories were also simplified on some assessment measures. Following this phase of the study, the parents/guardians of participants were invited to attend a focus group to provide feedback on their experiences and to suggest modifications to the study. Parents suggested that a picture be included on each weekly session outline to aid participants in remembering and applying the technique discussed that week. It was also recommended that participants be provided with a summary sheet at the end of the programme. The young women involved were asked for their feedback and they suggested that a certificate of participation be presented at the end of the intervention programme.

### Measures

The primary outcome measures explored in this study were strategies used to cope with pain and pain management knowledge. Secondary outcome measures quantified pain severity, pain interference, pain self-efficacy and pain-catastrophizing. Following delivery of the intervention, qualitative evaluation was conducted with stakeholders including group participants, parents/guardians, teachers, principals and/or staff members at Adult Day Centres to evaluate the programme and its impact. Various measures were administered at different time points – these are summarised in Table 1.

**Table 1 T1:** Outcome measures and time points

**Measure**	**Questionnaire**	**T1: Baseline/pre-intervention**	**T2: 5 weeks**	**T3: 10 weeks**	**T4: Post-intervention**	**T5: 12 week follow-up**
**Primary outcome measures**	Pain Coping Strategies	x			x	x
	Pain Coping Scenarios	x	x	x	x	x
	Pain Knowledge	x	x	x	x	x
**Secondary outcome measures**	Visual Analogue Scale [31]	x	x	x	x	x
	Modified version of the Brief Pain Inventory – Short Form [32]	x			x	x
**Process variables**	Modified version of the Self-Efficacy scale for child functioning despite chronic pain [33]	x			x	x
	Pain Catastrophizing Scale – Parent version (PCS-P) [23]	x			x	x
**Predictor variables**	Background Information Questionnaire	x				

#### Primary outcome measures

The Pain Coping Strategies Questionnaire [27] and the Pain Coping Scenarios Questionnaire (modified from McManus, [27]) were used to measure pain coping. These measures were previously compared pre-intervention, post-intervention and at 1-month follow-up, in a pilot study examining the feasibility and clinical utility of CBT for people with an intellectual disability [27]. On the Pain Coping Strategies Questionnaire, all participants showed an increase in wellness-focused coping strategies from pre-intervention to post-intervention assessment, however, these were generally not maintained at follow-up. On the Pain Coping Scenarios Questionnaire, 4 of the 5 participants showed an increase in wellness-focused coping strategies from pre-intervention to post-intervention assessment and this was maintained at follow-up for 3 participants.

On the Pain Coping Strategies Questionnaire, participants were asked to name all the different things they do to deal with their menstrual pain. Participant’s responses were coded as wellness-focused coping strategies or illness-focused coping strategies, based on the work of Jensen & Karoly [28]. Wellness-focused coping strategies included relaxation, exercise and distraction techniques. Illness-focused strategies included rest and use of medication. Coping strategies used were also coded as “behavioural” or “cognitive” in orientation, in line with the categorisation system used in the *Feeling Better* programme. The effectiveness of pain coping strategies was also assessed by asking participants to rate how well each of the strategies worked using three response options: “works very well”, “works sometimes”, “doesn’t work at all”. The Pain Coping Scenarios Questionnaire asked participants how they would cope with pain in four hypothetical situations i.e. during the night, at school/at their day programme, at home and during a social activity. This determined if participants could generalise techniques learnt during the intervention programme to situations in which they may experience menstrual pain. Again, coping strategies were coded as wellness-focused or illness-focused and as behavioural or cognitive in orientation. The Pain Knowledge Questionnaire [27] assessed knowledge of pain coping strategies using a seven item multiple choice questionnaire. Response options were “yes”, “no” and “don’t know”. The items on the scale reflect the core domains of the intervention e.g. relaxation, exercise, distraction, challenging negative thoughts. A clarifying question was asked following each correct answer (“Can you give me an example?”) to confirm that the participant had some knowledge related to their answer. If the participant answered the question correctly but the supplementary information provided demonstrated inaccuracies in knowledge, the response was not credited as correct.

The three primary outcome measures were administered at T1: baseline (pre-intervention), T4: 12 weeks from baseline (post-intervention) and T5: 3 months follow-up. Post intervention measures were administered by another researcher, independent of the research team, to minimise social desirability bias. The Pain Coping Scenarios Questionnaire and the Pain Knowledge Questionnaire were administered at two additional time points - T2: 5 weeks from baseline and T3: 10 weeks from baseline. These additional time point measures facilitated process evaluation to determine which elements of the intervention programme were most effective for this population.

#### Secondary outcome measures

Because variability in outcome measures across clinical trials hinders the evaluation of treatments, the Initiative on Methods, Measurement and Pain Assessment in Clinical Trials (IMMPACT) recommended that six core outcome domains should be considered when designing chronic pain clinical trials. These were defined as pain intensity, physical functioning, emotional functioning, participant ratings of improvement and satisfaction with treatment, symptoms and adverse events and participant disposition [29]. Pain, or pain intensity, is not the key target of the intervention in this study as the goal of CBT-based pain management programmes is not to reduce pain. Rather, it is to enhance adaptive coping and support the individual to resume a more productive and enjoyable life despite pain [29]. Lynch-Jordan et al. [30] demonstrated that the rate of change of functional disability was significantly more rapid than the change in pain intensity over the course of psychological treatment for children with chronic pain.

Participants rated pain intensity during their last menstrual period using a coloured Visual Analogue Scale (VAS) [31]. On this scale, 0 = no pain and 10 = lots of pain. Due to the challenges associated with using numerical rating scales with individuals with intellectual disabilities, proxy measures of pain severity were also obtained from the parents of participants. Pain interference was measured by a modified version of the Brief Pain Inventory – Short Form [32]. This questionnaire used a likert scale where 0 = did not interfere and 10 = completely interferes. The modified version of the Brief Pain Inventory – Short Form used in this study was specifically generated for the purpose of this research project. The specific modifications required included front and back female body outlines to enable participants to identify the areas of the body in which they experienced menstrual pain, omission of some questions e.g. questions regarding pain in the last 24 hours (participants may not be menstruating at the time of administration of questionnaires), changes to the questions on categories assessed (wording changes and additional categories included) and modifications to the response categories by including the use of a visual analogue rating scale in conjunction with a numerical rating scale. Modifications to the original Brief Pain Inventory – Short Form were required to enable it to be understood by and used with people with intellectual disabilities as well as to make it relevant to the assessment of menstrual pain, which is an intermittent rather than a constant type of pain.

Secondary outcome measures were administered to participants at T1: baseline (pre-intervention), T4:12 weeks from baseline (post-intervention) and T5: 3 months follow-up. Secondary outcome measures were administered to parents/guardians at T1, T4 and T5. The VAS was also administered to participants at T2: 5 weeks from baseline and T3: 10 weeks from baseline to determine the impact of the intervention on pain severity, over time.

## Supplementary research methodologies

### Moderator analyses

#### Process variables

Process variables are those which lead to change in the outcome measures. These included the level of cognitive ability of participants, pain self-efficacy and pain catastrophizing. Level of cognitive ability was confirmed by Team Leaders with reference to information recorded on the National Intellectual Disability Database (NIDD). The NIDD is a database of information about people who receive intellectual disability services in Ireland or who are in need of these services.

Pain self-efficacy refers to an individual’s belief that they can perform certain tasks related to school, friends and family even when they are in pain. It is an important variable to consider given its potential impact on participants’ willingness to implement strategies to cope with their pain. Participant pain self-efficacy was measured using a modified version of the self-efficacy scale for child functioning despite chronic pain [33], and was read to participants. Modifications included reducing the total number of items on the original scale and reducing the response options to three (1 = Always, 2 = Sometimes and 3 = Never).

Pain catastrophizing is a negative cognitive-affective response to anticipated or actual pain and has been consistently associated with pain intensity and pain related activity interference [34]. Pain catastrophizing was assessed using the parent version of the Pain Catastrophizing Scale (PCS-P) [23]. This is a thirteen item rating scale to assess parents’ thoughts and feelings when their child is in pain. The 5 response options are: not at all (disagree), mildly (agree), moderately (agree), severely (agree) and extremely (agree). Pain self-efficacy and pain-catastrophizing were assessed at the same time-points as the outcome variables i.e. T1: baseline (pre-intervention), T4:12 weeks from baseline (post-intervention) and T5: 3 months follow-up.

#### Predictor variables

There were a number of variables which may have moderated the impact of the outcome measures in this study. These included socio-demographics such as age, education etc.; time since onset of menstruation; frequency and duration of menstruation; number and frequency of menstrual symptoms experienced and history, treatment and use of medication to manage gynaecological problems and other medical conditions. Moderator analyses were conducted to examine the conditions under which moderating variables interacted with the intervention condition as predictor variables in the main effect analyses.

Pre- and post-intervention data collection has been completed. Data analysis is currently being conducted.

### Data analyses

#### Sample size and power calculation

There are a lack of well-conducted controlled trials and a lack of information about effect sizes of CBT with people with an intellectual disability within published research in this area. The authors were reliant on the few previous studies available regarding this area of research and for this reason, the feasibility study by Hassiotis et al. [35] was used as a guideline in calculating sample size requirement. This study proposed a total sample of 30 to be allocated across two conditions although there is currently discussion that feasibility trials ought to include up to 60 individuals. We based our sample size on the Hassiotis paper and allowed for 20% attrition, thus we recruited 36 participants across the treatment and control conditions, with n = 18 in each arm.

An *a priori* power analysis was conducted using G*Power [36]. With α = .05 (two-tailed), the proposed sample (*N* = 36) would detect moderate effects between groups (d = .50) with over 95% power using a repeated measures F test. A total sample of 16 participants would be needed to detect large effects (d = .8) with over 95% power using a repeated measures F test. For the regression analyses, a sample of 36 participants (α = .05) with three predictors would detect large effects (f^2^ = .35) with a power calculation of 80.95%, while six predictors would detect large effects with a power of 65.58%. The current sample was deemed appropriate as regression models with power less than 50% are deemed unreliable [37].

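### Recruiting 36 keeps the base of 30 only up to 16.7% attrition, not 20%, and the regression power that justifies the sample is quoted as if nobody is lost

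*Protocol article*

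**What the plan says.** Everything needed is in the protocol article, under Sample size and power calculation.

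- The base comes from an earlier feasibility study: "This study proposed a total sample of 30 to be allocated across two conditions".
- From that base the authors "allowed for 20% attrition, thus we recruited 36 participants across the treatment and control conditions, with n = 18 in each arm".
- For the group comparison, the 36 "would detect moderate effects between groups (d = .50) with over 95% power using a repeated measures F test".
- For large effects the statement solves for the sample instead: "A total sample of 16 participants would be needed to detect large effects (d = .8) with over 95% power".
- The regression power is given at the recruited number, in a sentence that opens "For the regression analyses, a sample of 36 participants (α = .05) with three predictors". At f² = .35 the stated power is 80.95% for those three and 65.58% for six.
- The section concludes: "The current sample was deemed appropriate as regression models with power less than 50% are deemed unreliable".

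No power figure is given for the number left after attrition.

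**The concern.** Two things do not fit together. First, an allowance for a loss fraction is made by dividing the target by one minus that fraction. Multiplying by one plus the fraction gives too few. The step from 30 to 36 matches the multiplication, so the stated protection against 20% loss is not delivered.

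Second, and more important, the section allows for loss and then evaluates power as if there were none. The regression figures carry the argument that the sample is adequate, and that argument is a comparison with a 50% limit. If the margin over the limit largely disappears at the number left after the allowed loss, a reader is given more reassurance than the plan supports.

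**Working it through.** **Inputs, all from Sample size and power calculation:** base total 30; attrition 20%; recruited 36 (18 per arm); α = .05; f² = .35; 3 or 6 predictors; stated power 80.95% and 65.58%; limit 50%.

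**Attrition**

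- 30 × 1.2 = 36, the recruited number. The article does not write the formula out; it is inferred from the exact match.
- Number needed to keep 30 after 20% loss: 30 / (1 − 0.20) = 37.5, so 38 (19 per arm).
- Number left from 36 after 20% loss: 36 × 0.80 = 28.8.
- Loss that 36 can absorb while keeping 30: 1 − 30/36 = 16.7%.
- Per arm: 18 × 0.80 = 14.4. Rounding down in each arm gives 28 in total; rounding the total 28.8 gives 29. Both are shown below.

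**Regression power**

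Overall F test of R² = 0 with p predictors: df1 = p, df2 = N − p − 1, noncentrality λ = f² × N. Power is the probability that this noncentral F exceeds the central F critical value at α = .05.

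| N analysed | λ | df2 (p = 3) | Power, p = 3 | df2 (p = 6) | Power, p = 6 |
|---|---|---|---|---|---|
| 36 | 12.60 | 32 | 80.95% | 29 | 65.58% |
| 30 | 10.50 | 26 | 71.3% | 23 | 53.8% |
| 29 | 10.15 | 25 | 69.4% | 22 | 51.6% |
| 28 | 9.80 | 24 | 67.4% | 21 | 49.4% |

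The first row reproduces both stated figures exactly, so the method is the one the authors used and the lower rows are comparable with it.

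**Margin over the 50% limit, six predictors**

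- At 36: 65.58 − 50 = 15.6 points above.
- At 29: 51.6 − 50 = 1.6 points above.
- At 28: 49.4 − 50 = 0.6 points below.

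The smallest N with at least 50% power for six predictors is 29.

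**What the inflation slip alone costs**

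Recruiting 38 would have left 38 × 0.80 = 30.4. At 30 analysed, six-predictor power is 53.8%, only 2.2 points more than at 29. Most of the difference from 65.58% therefore comes from quoting power at the recruited number, not from the two missing participants.

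**The case against.** The strongest defence has four parts.

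- **The base of 30 is a guideline, not a requirement.** It was borrowed from another feasibility study, and the article nowhere commits to 30 analysable participants. This stands, and it is one reason the inflation slip is small. But an allowance for attrition has meaning only relative to a number being protected, and 30 is the only candidate given.
- **The regression figures are correct and openly labelled as applying to 36.** This also stands. The fault is not in the calculation but in using these figures to call the sample appropriate directly after allowing for loss.
- **An allowance is not an expectation.** True: the article does not predict 20% loss. It does treat that loss as plausible enough to plan for, so power at that number belongs beside the power at 36.
- **This is a pilot with exploratory regression, and pre- and post-intervention data collection is reported as complete.** This limits the consequence and rules out recruiting more as a remedy. It does not make the stated protection right.

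Three stronger readings are tempting, and the documents do not support them.

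- A reader might infer that planned attrition takes the six-predictor model below the plan's limit. That holds only at 28, which is a loss of 8/36 = 22.2%. At 29 the limit is still met.
- A reader might infer that every power figure assumes 36. The d = .8 statement solves for a required total of 16, so the attrition allowance does not enter it.
- A reader might set the claim of over 95% power for d = .50 against a much lower between-group power after attrition and blame attrition for the gap. The article gives neither the within-person correlation nor the number of occasions used in that calculation. Assuming f = .25, a correlation of 0.5 and 3 or 5 occasions, the between-group test has 43–47% power at 36 and 34–38% at 28, so attrition accounts for only about 9 points. How d = .50 yields over 95% is a separate question.

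**Conclusion.** The point holds and is minor. The statement that 36 allows for 20% attrition is wrong by two participants: 36 covers 16.7%. The regression power used to justify the sample falls from 80.95% to 67–69% for three predictors and from 65.58% to 49–52% for six once the allowed loss is applied. That is about 12 to 14 points and 14 to 16 points respectively. The six-predictor model is then at about the plan's own 50% limit, with essentially no margin, but not clearly below it.

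These results rest on the article's own f² = .35 and α = .05, on the overall F test (confirmed by exact reproduction of both stated figures), and on 28 or 29 participants remaining. The number actually retained may differ and would supersede them.

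**What to change.** No further recruitment is called for. In the sample size section:

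1. State that 36 preserves 30 with up to 16.7% attrition, and that 20% attrition would leave about 29.
2. Beside the figures for 36, give regression power at 29 (69.4% for three predictors, 51.6% for six), noting 67.4% and 49.4% at 28. Better still, give it at the number actually retained, if known.
3. Reword the conclusion on adequacy to say that, after the allowed loss, the six-predictor model is at about the 50% limit.
4. Quote the power for d = .50 at the post-attrition number too, stating the assumed correlation, the number of occasions and the effect tested. The d = .8 statement needs no change on this account.

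The cost is a few sentences and one recalculation. The downside is that the stated figures become less favourable.

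### The stated power of over 95% is not supported for a between-group d of .50 at N = 36 or of .8 at N = 16; a between-groups repeated-measures test gives about 43–49% at an assumed correlation of .5

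*Protocol article*

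**What the plan says.** All of this is in the protocol article, under Sample size and power calculation, unless noted.

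- The sample comes from an earlier feasibility study that proposed 30 in total. The authors "allowed for 20% attrition", "thus we recruited 36 participants across the treatment and control conditions, with n = 18 in each arm".
- A G*Power calculation is then reported. "With α = .05 (two-tailed), the proposed sample" of 36 "would detect moderate effects between groups (d = .50) with over 95% power using a repeated measures F test".
- The next sentence reads: "A total sample of 16 participants would be needed to detect large effects (d = .8) with over 95% power", again for a repeated-measures F test.
- The statement does not give the type of repeated-measures test (between-groups or group-by-time interaction), the value of f, the number of occasions or the correlation between them.
- The schedule is under Primary outcome measures: "The three primary outcome measures were administered at T1: baseline (pre-intervention), T4: 12 weeks from baseline (post-intervention) and T5: 3 months follow-up". Two of the three measures also "were administered at two additional time points - T2: 5 weeks from baseline and T3: 10 weeks from baseline". Each primary measure therefore has 3 or 5 occasions.

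**The concern.** Only 18 per arm is a small sample for a standardised difference of .50. A plain two-sample t test has 31% power there, and 32% for d = .8 with 8 per arm. Repeated measurement helps a between-groups comparison only modestly when the occasions are correlated, so a rise to over 95% needs explaining.

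The Study aims ask whether the programme is more effective than usual care, and the Conclusion speaks of evaluating efficacy. Readers are told that the chance of missing a moderate effect is below 5%. If the real chance is around one half, a non-significant result could be misread as evidence that the programme does not work.

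**Working it through.** **Inputs from the article.** Alpha .05 two-tailed; N = 36 (18 per arm) with d = .50; N = 16 with d = .8; 3 or 5 occasions (m).

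**Assumptions, not in the article.** Correlation between occasions rho = .5, varied below; sphericity; equal arms.

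**Formulas** (noncentral F, two groups, G*Power parameterisation):
- Conversion for two equal groups: f = d/2, so d = .50 gives .25 and d = .8 gives .40.
- Between-groups test: λ = f²·N·m / (1 + (m − 1)·rho), df = 1 and N − 2.
- Group-by-time interaction: λ = f²·N·m / (1 − rho), df = m − 1 and (N − 2)(m − 1).

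**Step 1. Reproducing the printed figures.** Two routes can do it.

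| Route | m, rho | N = 36 (N = 34) | N = 16 (N = 14) |
|---|---|---|---|
| Between-groups, f set to d (.50, .80) | 3, .5 | 94.6% (93.3%) | 95.3% (91.9%) |
| | 4, .5 | 95.8% (94.7%) | 96.4% (93.4%) |
| | 5, .5 | 96.4% (95.4%) | 97.0% (94.3%) |
| Interaction, f = d/2 (.25, .40) | 3, .5 | 90.6% (88.8%) | 92.4% (87.8%) |
| | 3, .6 | 95.8% (94.7%) | 96.8% (94.1%) |
| | 4, .5 | 95.2% (93.9%) | 96.5% (93.5%) |
| | 5, .5 | 97.6% (96.8%) | 98.5% (96.6%) |

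Both routes can give over 95% at both sample sizes, with 16 as the smallest balanced total for the larger effect. The first does so at m = 4 or 5 with rho = .5. The second does so at m = 4 with rho = .5, or at m = 3 with rho = .6.

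**Step 2. Power for the effect as worded.** Between-groups test, f = d/2, rho = .5:
- d = .50, N = 36, m = 3: λ = .0625 × 36 × 3 / 2 = 3.375, power 43.1%.
- d = .50, N = 36, m = 5: λ = .0625 × 36 × 5 / 3 = 3.75, power 46.9%.
- d = .8, N = 16, m = 3: λ = .16 × 16 × 3 / 2 = 3.84, power 44.6%.
- d = .8, N = 16, m = 5: λ = .16 × 16 × 5 / 3 = 4.27, power 48.5%.

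Sensitivity at N = 36, m = 3 to 5: 51–59% at rho = .3 and 37–39% at rho = .7. Over m = 2 to 5 and rho from 0 to .9 the maximum is about 90% (N = 36) or 91% (N = 16), reached only with uncorrelated occasions. It never reaches 95%.

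At rho = .5, N = 36 gives 80% power at d of about 0.75 (m = 5) to 0.79 (m = 3). Reaching 95% for d = .50 would take about 128 (m = 5) to 142 (m = 3) participants in total. With 30 completers, power for d = .50 is 37–40%.

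**Step 3. Whether the interaction route rescues the statement.** Suppose the groups are equal at T1 and differ by d = .50 afterwards. The interaction f is the root mean square of the half-differences after centring over occasions. For T1, T4, T5 the half-differences are 0, .25, .25 with mean .167, so f = √[(.0278 + .0069 + .0069)/3] = .118. Then λ = .0139 × 36 × 3 / .5 = 3.0.

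| Pattern of the d = .50 difference | f | rho = .5 | rho = .7 | rho = .9 |
|---|---|---|---|---|
| 3 occasions, present at T4 and T5 | .118 | 31% | 49% | 93% |
| 5 occasions, present from T2 on | .100 | 28% | 46% | 94% |
| 5 occasions, present at T4 and T5 only | .122 | 41% | 65% | 99% |

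A gradual rise from T1 to T4 falls just below these, with f about .097 and 27% at rho = .5. An interaction f of .25 is therefore at least twice what a between-group d of .50 produces under these patterns.

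**The case against.** The strongest reply is that the authors may have made no conversion error. With the correct f = .25 and .40, the interaction test yields exactly 36 and 16 as the smallest balanced totals in two settings, one of them on the three-occasion schedule that all the primary measures share (at rho = .6). This stands. A reader might infer that d was typed in where G*Power expects f, and that the trial is really powered for d = 1.0 and 1.6. The article prints no f, test type, number of occasions or correlation, so it does not establish that. It is true that no measure has 4 occasions, and that at rho = .5 with 3 or 5 occasions only the d-as-f route gives over 95% at both sizes with 16 as the minimum. But rho = .5 is itself an assumption.

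It is also fair to say that 43–49% is conditional. At rho = .3 the between-groups power for d = .50 is 51–59%, so a flat claim that the trial would miss a moderate effect more often than not goes too far.

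Finally, the power figure did not set the sample size, the study is described as a pilot and exploratory, and data collection is complete. That limits the consequences. It does not make the printed figure right: entering f = .25 as an interaction answers a different question from the between-group d of .50 that the sentence names.

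**Conclusion.** The claim of over 95% power is wrong as written for the effect it names. For a between-group d of .50 at N = 36, the between-groups repeated-measures test gives about 43–47%, and for d = .8 at N = 16 about 45–49%, assuming rho = .5 and 3 to 5 occasions. Over rho .3 to .7 the N = 36 figure is about 37–59%. Under an interaction test, a d = .50 difference that emerges after baseline has roughly 28–41% power at rho = .5, and reaching 93% or more needs rho near .9, which is not stated.

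The conclusion does not depend on how the error arose, and the article does not settle that. Nor does it follow that 36 was the wrong number to recruit, since that number has a separate stated basis.

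**What to change.** Keep N = 36 and its justification from the feasibility study plus attrition. Then:

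1. Replace the power sentence with one that states the test type, f, number of occasions and correlation. For example: with N = 36 and two-sided alpha of .05, power for a between-group d of .50 (f = .25) is about 43–47% in a between-groups repeated-measures F test with 3 to 5 occasions and an assumed correlation of .5; 80% power is reached at d of about 0.75 to 0.8.
2. Delete the 16-participant sentence, or correct it to about 45–49% power for d = .8 on the same assumptions.
3. If an interaction test was intended, say so, and derive f from the expected pattern of group differences over time.
4. State that a non-significant result does not rule out a moderate effect, and report estimates with confidence intervals. Since analysis is under way, do this before results are interpreted.

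The cost is a few sentences and a much less favourable stated power. Recruitment and data are unaffected.
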